
**Fig. 4 Fig4:**
[figure not shown]
Time schedule of enrollment, interventions, and assessments

### Data collection

To facilitate researchers in observing and recording various indicators, we have organized the content—outcome measures, observation time points, adverse events, and safety evaluations—into a case report form (CRF). Researchers are required to follow the requirements of the CRF as well as fill in the relevant information in a timely and accurate manner.

### Quality control

To ensure the quality of this research, this pilot trial has undergone multiple modifications and revisions by relevant digestive disease specialists, acupuncture experts, professional statisticians, and research methodologists. Strict inclusion and exclusion criteria have been established. To maintain data objectivity, we will ensure that the statisticians and evaluators were blinded. All researchers, and particularly APP operators, have completed our training, thereby ensuring consistent treatment practices and uniformity in the terminology used for communication with the subjects. All operators have a diploma in Chinese Medicine, and they were trained uniformly—before subject recruitment—to pass a test based on the operational protocol. The drugs and materials used in this research have been purchased uniformly; thus, we can ensure that our conclusions will be reliable. The CRF is filled in strictly and in accordance with the CRF instructions; in addition, detailed data regarding subject observations are being recorded. We require the researchers to be conscientious and thorough during data entry, and a corresponding evaluation report is attached. Original data cannot be altered; if modifications are made, these will be explained in detail and accompanied by the signature of the staff member who made the change.

This study involves a two-level quality inspection system. Level 1 involves a quality control inspection. Quality inspectors will be appointed by the study leader; they will design a quality checklist and monitor the records of all original data, data reports, and adverse events in accordance with that checklist. Level 2 involves quality supervision. The quality supervisor will be appointed directly by the study leader. The supervisor will (1) monitor the research operators’ command of the research design and process; (2) confirm the authenticity, accuracy, and integrity of all research data records, reports, and CRF; and (3) ensure consistency in the original data.

### Sample size estimation and statistical analysis

#### Sample size estimation

This study consists of two groups; the sample size-estimation formula is therefore based on a two-group, parallel, controlled design:$$ n=\frac{{\left({\mathrm{Z}}_{1-a/2}+{\mathrm{Z}}_{1-\beta}\right)}^2\times \left({\sigma}_1^2+{\sigma}_2^2\right)}{\delta^2}, $$where *n* represents the sample size in each group, σ represents the standard deviation, and *δ* represents the between-group difference with clinical significance. At an α value of 0.05, a power of 80 %, and given a two-sided test, we obtained Z scores of Z_1 − *a*/2_ = 1.96 and Z_1 − *β*_ = 0.84 from the Z score table. Eight subjects recruited from November 2015 to December 2015 were included in the pilot trial, and the primary outcome measure was the time to first flatus: *S*_1_ = 3.14 and *S*_2_ = 5.58. A decrease of 4 h in the time to first flatus was set as our clinical expectation based on preliminary tests and clinical experience. The above data were used to estimate the value of the overall parameter to be inserted into the above formula, and an n-value of 20.09 was obtained. Therefore, the rounded sample size in each group was 21; assuming a 15 % dropout rate, the final sample sizes in the experimental and control groups would be 25 cases, yielding the required 50 cases.

#### Statistical analysis

Content of statistical analysisSample distribution: The absolute number of dropouts as well as the rate will be described for each data set. These data will be analyzed, and the reasons for each termination are listed in detail.Balance comparison: The subjects’ general information will be compared to assess the comparability of the two groups.Efficacy analysis: The subjects’ time to first passage of flatus will be used as the primary outcome measure to evaluate the efficacy and safety of APP in treating gastrointestinal dysfunction after laparoscopic cholecystectomy. The means and standard deviations will be calculated to describe the outcome measure, and the experimental and control groups will be statistically compared using two independent-sample *t* tests. The subjects’ time to first defecation, abdominal pain, abdominal distention, nausea, vomiting, mental status, and quality of life—i.e., the seven secondary outcome measures—will be used to evaluate the efficacy of the APP. Six of these—namely, the time to first defecation, abdominal pain, abdominal distention, nausea, vomiting, and quality of life—will be described using mean ± standard deviation. The scores for mental status will be recorded and categorized in terms of the classification criteria. The statistical analysis of time to first defecation is the same as that of time to first passage of flatus; abdominal pain, abdominal distention, nausea, vomiting, and quality of life will be statistically compared between groups using Repeated Measures Analysis of Variance (RMANOVA). However, before the RMANOVA is performed, a sphericity test will be used to determine whether the data are suitable for analysis using RMANOVA. If the data do not meet the conditions of sphericity, the correction factor *ε* will be used to correct the degree of freedom before the RMANOVA is performed. The categorical measure of mental status will be analyzed using either the rank-sum test or Spearman’s rank correlation.Safety analysis: In accordance with the above definitions of adverse events, we compiled a list describing, grading, and explaining the adverse events in detail. We will ascertain descriptive statistics of the absolute number—as well as the incidence—of each adverse event in both groups. When making comparisons, we will use the *χ*^2^ test or Fisher’s exact test for statistical analysis.Methods of statistical analysisData will be analyzed in accordance with the principle of intention-to-treat (ITT). That is, we will include all subjects who were treated at least once in the trial. Efficacy and safety measures will be analyzed in accordance with “per-protocol” (PP), whereby we will include all subjects who completed the entire trial and followed the protocol requirements. Quantitative variables in the trial data will be expressed as $$ \overline{\mathrm{X}}\pm \mathrm{S}\mathrm{D} $$ for statistical description, whereas qualitative variables will be recorded as the number of cases in each category. If the quantitative variables constitute repeated measures data, then RMANOVA will be used for comparison, and the sphericity test will be used to determine the suitability of, as well as to correct, the data. Qualitative variables will be analyzed using either the rank-sum test or Spearman’s rank correlation; count data for incidence will be compared using the *χ*^2^ test or Fisher’s exact test. All statistical tests are two-sided, and differences with *P* values < 0.05 will be considered statistically significant. Statistical analysis will be performed using SPSS 19.0 statistical software for calculations.

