## Background

Gastrointestinal dysfunction is a common complication of abdominal surgery; its main symptoms include delayed flatus and defecation, abdominal distention, abdominal pain, nausea, and vomiting. Therefore, promoting rapid recovery from gastrointestinal function has become integral to postoperative rehabilitation [1]. Gastric motility typically recovers within 24–48 h after surgery, whereas colonic motility is generally restored within 48–72 h [2]. Thus, it often takes 2–3 days for the patient to recover from gastrointestinal dysfunction. Postoperative gastrointestinal dysfunction is usually treated using alvimopan; however, this drug has adverse effects such as nausea and vomiting [3].

Auricular point acupressure (APP) may be a noninvasive physical treatment for the condition of postoperative gastronintestinal dysfunction [4, 5]. This therapy involves stimulating sensitive points on the auricle using vaccaria seeds; the points correspond to specific organs. In previous studies, we compared subjects’ postoperative time to flatus between an experimental group that received APP using vaccaria seeds on the large intestine point (CO7; 20.19 ± 3.14) and a control group that received APP sham stimulation (30.82 ± 5.58). Preliminary results showed that the APP using vaccaria seeds on CO7 can promote the recovery of gastrointestinal motility after abdominal surgery.

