### Intervention

After surgery, all the included subjects will lie in the supine position without a pillow and fast. The subjects will be given a liquid diet on the day after surgery. The APP therapy (or sham therapy) will be performed 6 h after the operation and every 12 h subsequently, for six treatment sessions, each lasting 3 min. The first evaluation will be performed 6 h after the operation, immediately before the first treatment. The patients will be then evaluated once every 12 h, for seven evaluations. The acupuncture points will be selected on the basis of the Nogier auricular point diagram [8]. Specifically, CO7 will be selected (the anterior 1/3 between the helix crus/part of the helix and the AB line, i.e., the auricular concha zone 7; Fig. 2). Operators will bring the required tools to the subject’s bedside and help the subject assume a comfortable position. The operator will then hold the upper posterior corner of the helix with one hand, and find the sensitive points with an auricular point detector (XS-100A; Guangzhou City Strong Medical Technology Co. Ltd., Guangzhou, China) using the other hand. The area will be disinfected using 75 % alcohol, and the vaccaria seeds will be attached to the auricular points.

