
## Discussion

Anesthesia, carbon dioxide pneumoperitoneum, surgical trauma, inflammation, postoperative bed rest, and other factors can cause postoperative gastrointestinal dysfunction in LC patients. Such adverse effects can lead to prolonged hospitalization, prevent patients from recovering functionally, and increase the medical burden.

Currently, postoperative gastrointestinal dysfunction is treated using postoperative fasting, gastrointestinal decompression, early ambulation, enema, chewing gum, gastroprokinetic drugs, and early enteral nutrition [14–16]. In this regard, APP using vaccaria seeds has clear benefits for patients with diseases of the digestive system [17, 18]. This study is the first standardized, scientific, clinical trial to evaluate the efficacy and safety of APP treatment using vaccaria seeds for postoperative gastrointestinal dysfunction. The study was prompted by long-term clinical experience and will use the time to first passage of flatus as the primary outcome measure. We wish to provide a scientific basis upon which to promote this therapy.

A systematic review [1] showed that the time to first passage of flatus has important clinical significance in terms of recovering gastrointestinal motility, and the same parameter is closely related to the recovery of the postoperative gastrointestinal dysfunction. For this reason, most clinical trials addressing the treatment of postoperative gastrointestinal dysfunction, such as that by Cho in 2015 [19] and that by Kim in the same year [20], use the time to first passage of flatus as a primary outcome. In this way, they can evaluate the recovery of gastrointestinal function. Hence, we also have set this measure as the primary outcome in our trial. During the perioperative period, subjects may exhibit psychological changes such as anxiety and depression [21]; thus, the subjects’ anxiety and depression will be used as secondary indicators of recovery. Furthermore, subjects’ quality of life within a month of discharge can also indicate the longer-term effects of this therapy.

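### Classical RMANOVA discards every subject with a missing evaluation, so five secondary outcomes cannot be analysed in the intention-to-treat set that the plan defines

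*Protocol article*

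**What the plan says.** All places are in the protocol article.

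- **Test.** Under Statistical analysis: "abdominal pain, abdominal distention, nausea, vomiting, and quality of life will be statistically compared between groups using Repeated Measures Analysis of Variance (RMANOVA"). A sphericity test comes first, and the remedy for failing it starts "If the data do not meet the conditions of sphericity, the correction factor", applied to the degrees of freedom. The software is SPSS 19.0.
- **Schedule of the four symptom outcomes.** Under Intervention: "The first evaluation will be performed 6 h after the operation, immediately before the first treatment", and then "The patients will be then evaluated once every 12 h, for seven evaluations". Treatment is given at 6 h and "every 12 h subsequently, for six treatment sessions, each lasting 3 min".
- **Schedule of quality of life.** Under Outcome measures, the GIQLI is taken three times: 24 h before surgery, 2 weeks after discharge and 1 month after discharge.
- **Populations.** Under Statistical analysis, ITT means everyone treated at least once. Per-protocol means those who completed the trial and followed the protocol.
- **Expected loss.** Under Sample size estimation: "assuming a 15 % dropout rate, the final sample sizes in the experimental and control groups would be 25 cases".
- **Incomplete subjects.** Statistical analysis has the number, rate and reasons of dropouts described. Elimination criteria takes out of the study those who, among other reasons, stop treatment, have serious complications, miss follow-up or give incomplete information.

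**The concern.** The plan fixes a test and a population that do not fit together. The classical repeated-measures procedure works on one full vector per subject. The ε correction adjusts degrees of freedom for unequal variances of differences and does nothing about gaps. A subject with six of seven pain scores is in the ITT set by definition, yet contributes nothing to the ITT test of pain.

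Five of the seven secondary outcomes depend on this test: pain, distention, nausea, vomiting and quality of life. Time to first defecation and mental status are analysed by other methods. What is at stake is precision in a trial of 50 subjects, an analysis labelled ITT that is in fact a completer analysis, and exposure to bias if the reasons for missing evaluations are related to recovery.

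**Working it through.** **Inputs from the article.** α 0.05 two-sided, power 80%, SDs 3.14 and 5.58 h, difference 4 h, dropout 15%, 25 per arm (Sample size estimation); first evaluation at 6 h, seven evaluations 12 h apart, six sessions (Intervention); three GIQLI assessments (Outcome measures).

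**1. The plan's own sample size.**
n = (1.96 + 0.84)² × (3.14² + 5.58²) / 4² = 7.84 × 40.996 / 16 = 20.09, rounded up to 21. With dropout, 21 / 0.85 = 24.7, so 25 per arm and 50 in all. The stated figures reproduce. They were derived for time to first flatus, not for the repeated outcomes.

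**2. The schedule.** Evaluations fall at 6, 18, 30, 42, 54, 66 and 78 h (6 + 6 × 12 = 78). Sessions run from 6 to 66 h (6 + 5 × 12 = 66).

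**3. Test against population.**

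| Subject | In ITT set? | Used by classical RMANOVA? |
|---|---|---|
| All 7 symptom evaluations | yes | yes |
| 6 of 7 evaluations | yes | no |
| Last seen at 48 h (4 of 7) | yes | no, all 4 discarded |
| Both earlier GIQLI scores, 1-month score missing | yes | no for GIQLI |

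**4. Loss at the plan's own dropout rate.** 25 × (1 − 0.15) = 21.25, so about 21 per arm. The standard error of a between-group comparison rises by √(25/21) = 1.09, about 9%. The detectable standardized difference for one comparison at 80% power is (1.96 + 0.84) × √(2/m):
- m = 25: 0.79
- m = 21: 0.86

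The 9% is the most that an available-data analysis could win back at this dropout rate. Dropouts contribute part of a series, and someone with no evaluation after the first session adds almost nothing to the comparison.

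**5. Scattered missed evaluations.** The article gives no rate. Assume that each evaluation is missed independently with probability p, in the absence of dropout. The share with all seven is (1 − p)⁷:
- p = 3%: 81% complete, about 20 of 25 per arm
- p = 5%: 70% complete, about 17 of 25 per arm, detectable difference 0.96

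If p = 5% came on top of 15% dropout, 25 × 0.85 × 0.698 = 14.8, so about 15 per arm would be complete. For the GIQLI with three assessments and p = 5%, 0.95³ = 0.857, or about 21 per arm from this source alone. Its exposure is smaller, but two of its three assessments come after discharge.

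**The case against.** **The loss is already budgeted.** The design aims at 21 per arm after dropout, so 42 completers is the plan. This stands: dropout alone does not push the analysis below the planned number. It does not justify discarding data already collected, and scattered gaps are not in the budget.

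**Efficacy is also to be analysed per protocol, in completers.** Complete-case RMANOVA fits that set, and a subject who leaves before 66 h misses a session and falls outside it anyway. This stands too and narrows the point to the ITT analysis.

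**A missing-data rule may be in a fuller document.** It may, and its absence from the article is not the point. The article itself commits to the test and to the population. RMANOVA could run on the ITT set only after gaps are filled, and no such step is named.

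**The tempting stronger reading.** A reader might infer that treated subjects recover and go home before 78 h, so that the completer analysis selects slow recoverers, more so in the acupressure arm, and shrinks the effect. The Background does say "Thus, it often takes 2–3 days for the patient to recover from gastrointestinal dysfunction", and the Discussion says of gastrointestinal dysfunction that "Such adverse effects can lead to prolonged hospitalization, prevent patients from recovering functionally, and increase the medical burden". But that sentence is general background. No length of stay or discharge rule is given, and bedside sessions up to 66 h imply a stay of about that length. Subjects and families are helped to record the symptom scores, and nothing ends this at discharge. Removals under Elimination criteria for conversion to laparotomy or serious complications would instead leave the better recoverers. The direction is therefore undetermined. Any bias figure would rest on an invented discharge rule and invented score distributions, so none is given here.

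**Conclusion.** The point holds as a mismatch between method and population. For five of the seven secondary outcomes, the named RMANOVA cannot analyse the ITT set defined in the same section and turns it into a completer analysis.

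On the plan's figures the size is modest: about 21 instead of 25 per arm, a standard error about 9% larger, and a detectable standardized difference of 0.86 instead of 0.79. Larger losses depend on the assumed rates of scattered missed evaluations. The result rests on two premises: the procedure is the classical one, as the sphericity test and ε correction indicate, and gaps are not filled beforehand.

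Bias is a risk if missingness is tied to recovery, whether through early discharge or through removals for complications. Its presence, size and direction cannot be established from the article. The primary outcome, compared by t test, is unaffected. The change is worth making because it is cheap and makes the analysis match its label.

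**What to change.** - **Statistical analysis, continuous outcomes.** Replace RMANOVA for pain, distention, nausea and GIQLI by a linear mixed model for repeated measures (SPSS MIXED) with group, time and their interaction, using every available evaluation from every subject in the ITT set as the article defines it. State the covariance structure in advance. An unstructured matrix over seven times has 7 × 8 / 2 = 28 parameters, which is many for at most 50 subjects, so name compound symmetry as the fallback.
- **Vomiting.** Use a corresponding count model on the available evaluations.
- **Per-protocol.** Keep the completer analysis as the per-protocol sensitivity analysis.
- **Elimination criteria.** Reconcile the removal of subjects with incomplete information with the ITT definition, so that data already collected from them stay in the ITT analysis. This concerns the use of data only.

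**Cost.** Some rewording and slightly more analysis work, with no extra patients or procedures. SPSS 19.0 already contains the mixed procedure. Recruitment is described as ongoing, so the change can be fixed before analysis. The model relies on data being missing at random, which should be stated. That is a weaker assumption than the completer analysis needs, but it still cannot be verified from the data.

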### Outcome measures and participant timeline

#### Outcome measures

Baseline dataDemographic data will be recorded using a general information questionnaire, which we designed in house. The questionnaire includes questions on age, gender, education, occupation, weight, and height.Clinical characteristics will be recorded using another in-house-designed questionnaire. Specifically, data will be collected on the surgery time, anesthesia time, intraoperative blood loss, intraoperative fluid transfusion volume, and vital signs (temperature, heart rate, respiratory rate, and blood pressure).Primary outcome measureThe primary outcome is the time to first passage of flatus—we will begin observing and recording when subjects return safely to the ward, and the subjects and their families will be asked to record the time of the first passage of flatus. The interval between the two time points will be then calculated.Secondary outcome measuresTime to first defecation: We will observe and record when the subjects return safely to the ward, and the subjects and their families will be asked to record the time of first defecation. The interval between the two time points will then be calculated.Abdominal pain: The subjects’ degree of postoperative pain will be assessed using the VAS scale [10]. The first evaluation will be performed 6 h after surgery, immediately before the first treatment. Evaluations will then be carried out once every 12 h, for seven evaluations. Assistance will be given to subjects and their families in recording this information.Abdominal distention: The Likert scale will be used to assess the subjects’ degree of postoperative abdominal distention [11]. The first evaluation will be performed 6 h after the surgery, immediately before the first treatment. Evaluations will then be carried out once every 12 h, for seven evaluations. Assistance will be given to subjects and their families in recording this data.Nausea: The VAS scale will be used to assess subjects’ degree of postoperative nausea [10]. The first evaluation will be performed 6 h after the surgery, immediately before the first treatment. Evaluations will then be carried out once every 12 h, for seven evaluations. Assistance will be given to subjects and their families in recording this data.Vomiting: The frequency of postoperative vomiting will be recorded. The first evaluation will be performed 6 h after the surgery, immediately before the first treatment. Evaluations will then be carried out once every 12 h, for seven evaluations. Assistance will be given to subjects and their families in recording this data.Mental status: The Hospital Anxiety and Depression Scale (HADS) will be used to assess the subjects’ postoperative mental status [12]. The HADS consists of 14 items: seven assess depression, and the other seven assess anxiety. The scores of the anxiety and depression subscales are classified as follows: 0–7 points indicate no symptoms, 8–10 points indicate suspected symptoms, and 11–21 points indicate confirmed symptoms. The first evaluation will be performed 24 h before surgery, and the second evaluation will be performed on the day of discharge.Quality of life: the Gastrointestinal Quality of Life Index (GIQLI) will be used in this study [13]. The GIQLI aims to measure the quality of life of subjects with digestive diseases and includes five domains: subjective symptoms, physiological functional status, daily life, social activities, and psychological and emotional state. Within these domains, 36 items are assessed, each with a score from 0 to 4 points, for a total possible score of 144 points. The normal population will score 12–125 points. The first evaluation will be performed 24 h before surgery, and the second will be conducted 2 weeks after discharge. A follow-up evaluation will be carried out 1 month after discharge. Higher scores indicate better health status.Safety indicatorsAn event can be defined as an adverse event if at least four subjects suffer a symptom—such as local skin allergies, dizziness, and low blood sugar—during the treatment-evaluation period. These events will be statistically analyzed, and treatment safety is evaluated on this basis, in accordance with the research protocol. If serious adverse events occur, they will be immediately reported and managed accordingly.Participant timelineFor a complete overview of the time schedule of enrollment, interventions, and assessment for participants, see Fig. 4.

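### RMANOVA for five secondary outcomes makes no adjustment for the pre-treatment evaluation already collected and leaves the treatment contrast unnamed

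*Protocol article*

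**What the plan says.** The statistical analysis section of the protocol article assigns one method to five of the seven secondary outcomes: "abdominal pain, abdominal distention, nausea, vomiting, and quality of life will be statistically compared between groups using Repeated Measures Analysis of Variance (RMANOVA"). It adds a sphericity test and an epsilon correction of the degrees of freedom. It names no baseline covariate, no change score and no removal of the first evaluation, and it does not say which RMANOVA term tests the treatment.

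The outcome measures section fixes the timing:

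- Pain: "The first evaluation will be performed 6 h after surgery, immediately before the first treatment".
- Distention, nausea and vomiting: "The first evaluation will be performed 6 h after the surgery, immediately before the first treatment".
- All four symptoms: "Evaluations will then be carried out once every 12 h, for seven evaluations". The intervention section plans the treatment "for six treatment sessions, each lasting 3 min", which fits one evaluation before treatment and six after it has begun.
- GIQLI: "The first evaluation will be performed 24 h before surgery, and the second will be conducted 2 weeks after discharge", and then "A follow-up evaluation will be carried out 1 month after discharge". That makes three evaluations, one of them before treatment.

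Vomiting is a count ("Vomiting: The frequency of postoperative vomiting will be recorded"), but it is to be summarised by mean and SD and analysed by RMANOVA.

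**The concern.** Randomised groups cannot differ because of treatment at an evaluation made before treatment. If that evaluation is one level of the time factor, the group main effect averages a true zero with the post-treatment differences, so it understates the effect. If it is dropped, its power to explain between-patient variation is lost. Either way, information already collected is not used for the purpose it serves best.

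The unnamed contrast is a second weakness. RMANOVA gives a group test and a group-by-time test, and they answer different questions with different power. A plan that names neither leaves the choice open until the data are seen.

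For vomiting, a mean with SD and a normal-theory model describe a count poorly.

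At stake are the precision and interpretability of five secondary outcomes in a trial of 50 patients.

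**Working it through.** **The plan's own figure.** The only sample size given is for the primary outcome: (1.96 + 0.84)² × (3.14² + 5.58²) / 4² = 20.09, rounded up to 21 per group; 21 / 0.85 = 24.7, hence 25 per group and 50 in total. This reproduces and is not affected. The protocol gives no power or effect size for the RMANOVA outcomes.

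**Inputs from the protocol.** T = 7 evaluations for symptoms and T = 3 for GIQLI, one before treatment in each case, so m = T − 1 = 6 and 2; n = 21 per arm; two-sided alpha 0.05.

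**Assumptions, because the protocol gives no values.** Unit variance at each evaluation, equal correlation r between any two evaluations (compound symmetry), and a constant effect δ = 0.5 SD after treatment starts.

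**Dilution.** The group main effect estimates (m/T)δ: 6/7 = 0.857 for symptoms and 2/3 = 0.667 for GIQLI. This needs no correlation.

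**Variance of each patient's summary:**

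- mean of all T evaluations: (1 + (T − 1)r)/T
- mean of the m post-treatment evaluations: (1 + (m − 1)r)/m
- the same, adjusted for baseline: (1 + (m − 1)r)/m − r²

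The noncentrality of each t test is contrast / √(variance × 2/21). For the interaction F test it is (21/2) × Σ(δₜ − mean δ)² / (1 − r).

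**Results at r = 0.5:**

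| Test | Contrast | Variance | Noncentrality | Power |
|---|---|---|---|---|
| Seven evaluations, main effect | 0.429 | 0.571 | 1.84 | 43% |
| Seven, interaction (6 and 240 df) | – | – | 4.50 | 30% |
| Seven, post-treatment only, unadjusted | 0.500 | 0.583 | 2.12 | 54% |
| Seven, baseline-adjusted | 0.500 | 0.333 | 2.81 | 78% |
| GIQLI, main effect | 0.333 | 0.667 | 1.32 | 25% |
| GIQLI, interaction (2 and 80 df) | – | – | 3.50 | 36% |
| GIQLI, post-treatment only, unadjusted | 0.500 | 0.750 | 1.87 | 45% |
| GIQLI, baseline-adjusted | 0.500 | 0.500 | 2.29 | 61% |

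**Sample-size ratio**, main effect relative to baseline-adjusted, = [variance over all T / (m/T)²] / adjusted variance:

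| r | Seven evaluations | GIQLI |
|---|---|---|
| 0.1 | 1.30 | 1.67 |
| 0.3 | 1.67 | 2.14 |
| 0.5 | 2.33 | 3.00 |
| 0.7 | 3.89 | 5.00 |

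At r = 0.5 the ratio splits into 1.33 × 1.75 for seven evaluations and 2.0 × 1.5 for GIQLI. The first factor is the cost of averaging the baseline in, the second the cost of not adjusting for it.

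**A non-constant effect.** Take r = 0.5, 21 per arm and a peak of 0.8 SD, with fractions 0, 0.5, 1, 1, 0.5, 0, 0 of that peak over the seven evaluations. The post-treatment average is 0.4 SD; the interaction test has 87% power and the baseline-adjusted average 59%. For an effect growing linearly to 0.8 SD the figures are 65% and 72%.

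**Vomiting.** Sparse, overdispersed counts were simulated without a treatment effect (assumed rates, 21 per arm, 3000 runs per setting). The main-effect test rejected in 4.1% to 4.6% of runs, the uncorrected interaction in 8% to 10%, and the epsilon-corrected interaction in about 3%.

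**The case against.** **The baseline may not be a time level.** The protocol does not say that it is. The sphericity step supports that reading for GIQLI, because without the baseline only two levels remain and sphericity is trivial. It does not help for the symptoms, where six levels would remain. The handling of baseline and the choice of contrast might also be set out in an analysis plan that is not shown. What survives is that the article does fix the method, without adjustment, and that dropping the first evaluation still gives 54% against 78%, or 45% against 61% for GIQLI.

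**The dilution is not a property of every RMANOVA test.** A reader might infer that the whole analysis shrinks the effect to 6/7 or 2/3. It does not: that holds for the group main effect only. The interaction is nevertheless weaker than baseline adjustment in the constant-effect cases computed.

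**Baseline adjustment is not uniformly more powerful.** This stands. The background section says recovery often takes 2–3 days, so the groups could converge before 78 h, and the transient example favours the interaction test.

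**Vomiting.** A reader might infer that the F tests give false positives. The simulation does not show this for the main-effect or the epsilon-corrected test, and the plan prescribes the correction when sphericity fails. Sparsity is itself an assumption, and the normal-theory power figures do not carry over to this count.

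**Missing visits.** If 5% of values were missing independently at each visit, 1 − 0.95⁷ = 30% of patients would lack a complete set of seven. The protocol gives no such rate, only 15% dropout, so nothing here rests on that figure.

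**Schedule.** If seven evaluations follow the first, the dilution is 7/8, not 6/7.

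**Conclusion.** The point holds as a matter of efficiency and clarity. Five secondary outcomes are compared by RMANOVA without adjustment for a pre-treatment value that is already collected, and the treatment contrast is not named. Under the stated assumptions at r = 0.5, none of the three readings of the plan exceeds 54% power for seven evaluations or 45% for GIQLI, against 78% and 61% with adjustment. The size of the gain depends on the correlation: relative to the main-effect test, the sample-size ratio runs from about 1.3 to 3.9 for seven evaluations and from 1.7 to 5.0 for GIQLI as r goes from 0.1 to 0.7. The ranking against the interaction test also depends on a roughly constant effect.

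The vomiting point is minor: the method suits a count poorly, but no inflated error rate is shown for the main-effect or epsilon-corrected tests. The primary t test and the sample size are untouched, and no bias toward a false positive result has been shown.

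**What to change.** For pain, distention, nausea and GIQLI, fit a linear mixed model to the post-treatment evaluations only, with the pre-treatment value as covariate and group, time and group-by-time as terms. Name the average group difference over the post-treatment evaluations, with its 95% CI, as the treatment contrast. Report group-by-time as well, since it would show a transient effect that the average could miss.

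For vomiting, compare total post-treatment episodes between groups by a rank-sum test or negative binomial regression.

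The cost is wording in the statistical section. No new data, visits or patients are needed. The article reports recruitment as ongoing, so the change should be recorded before the data are unblinded.
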